#### Secondary outcome (i): immediate within-treatment changes in pain and strength

Since it is anticipated that the isometric exercise group may demonstrate greater immediate improvements in pain and strength, with a faster return to function, compared to either the isotonic concentric or isotonic eccentric groups, a key secondary outcome is to explore between-group within-treatment immediate changes in pain and strength during the rotator cuff strengthening component of the physiotherapy intervention. Measures of pain and strength will therefore be undertaken during treatment session 2 and 3 using a VRS (during shoulder motion) and hand-held dynamometer (resisted internal and external rotation) before and after completion of the intervention: a set of external (treatment 2) and internal (treatment 3) rotation contractions undertaken as per the group-specific contraction type (isometric/isotonic concentric/isotonic eccentric). All strength tests will be performed with the Commander Power track II hand-held dynamometer (JTech Medical). Each test will be performed as a “make” test, with the participant exerting a maximal isometric contraction against the dynamometer being held stationary by the tester [49–51]. For the dynamometer testing, participants will be tested in a standardised standing position—feet shoulder width apart, hips and knees in slight flexion, elbows flexed to 90° by the side of but not touching the body and wrist in neutral (palm facing midline) [49]. The test will be repeated twice with a rest of 5 s between tests [51].

#### Secondary outcome (ii): shoulder-related symptoms and disability

Shoulder-related symptoms and disability will be measured using the Western Ontario Rotator Cuff Index (WORC) and the Shoulder Pain and Disability Index (SPADI). Patient-reported outcome measures are increasingly recommended [52], and their use in patients with shoulder disorders have been investigated in several systematic reviews [53–56]. Both the SPADI and WORC have been shown to have good psychometric qualities that can be used for assessing individuals with shoulder pain including rotator cuff disorders [54]. Further, the WORC has been shown to be one of the most responsive questionnaires for patients suffering from rotator cuff disorders [54]. These outcome measures will be assessed at baseline, week 6, week 12 and via postal review at 6 months.

#### Secondary outcome (iii): perception of pain (current/usual/night)

Usual, current and night pain will be measured using an 11-point NRS. This will be undertaken at baseline, week 6 and week 12.

#### Secondary outcome (iv): shoulder muscle strength

Shoulder muscle strength will be assessed in varying test positions. As well as the within-treatment internal and external rotation in neutral test positions described above (secondary outcome (i)), three additional test positions will be undertaken at the main assessment points (baseline, week 6 and week 12). These will include shoulder abduction, external rotation at 90° and the empty can position, again using a hand-held dynamometer. Each test will be performed as a “make” test in the standardised standing position described above, held for 5 s and repeated twice [49–51].

#### Secondary outcome (v): perceived global rating of change score

Perceived change will be measured using a global rating of change score (GRCS) based on a 5-point Likert scale (much worse, slightly worse, no change, slightly better, much better) allowing patients to rate their perceived change following the intervention. Though criticised because of the need to recall baseline health status, GRCSs are commonly used to evaluate patient-perceived change in studies investigating interventions for shoulder pain [56] and have been shown to be clinically relevant, enabling interpretation of meaningful change in pain from a patient perspective [57]. The GRCS will be measured at the secondary end-point of the study (week 12).

### Physiotherapy intervention

The physiotherapy intervention will involve two treatment phases. In Phase 1, participants will attend on four consecutive weekly occasions for one-on-one treatment sessions with the physiotherapist. The intervention is exercise-based and aims to address (i) altered scapulo-humeral movement patterns, (ii) rotator cuff strengthening and (iii) upper quadrant flexibility/building posterior musculature (see Table 1). Participants will be taught the exercises at each visit with the intervention progressing in the following stages:

**Table 1 Tab1:** Physiotherapy intervention overview

Treatment		Aim	Exercise	Description
Session 1	Retrain scapular movement patterns.	Scapular stability/retraining: optimise the position of the scapular and humeral head during shoulder motion, restoring normal scapulo-humeral rhythm.	Scapular setting. Scapular shrugs.	Scapular setting in standing at 0° with scapular rotation/ tilt correction (based on individual deficits). Build scapular stability-progression to scapular shrugs.
Session 2	Improve rotator cuff strength.	Improve rotator cuff strength (in optimal scapulo-humeral movement pattern).	Shoulder external rotation strengthening in neutral.	External rotation in standing with elastic (isotonic) or rigid (isometric) resistance band. Shoulder adducted to side and elbow at 90°.
Session 3	Improve rotator cuff strength.	Improve rotator cuff strength (in optimal scapulo-humeral movement pattern).	Shoulder internal rotation strengthening in neutral.	Internal rotation in standing with elastic (isotonic) or rigid (isometric) resistance band. Shoulder adducted to side and elbow at 90°.
Session 4	Build posterior musculature and restore flexibility.	Improve posterior muscle strength.	Standing rows at 45° or 90°.	Bilateral standing rows progressing from 45° to 90° shoulder abduction with resistance band.
		Improve flexibility of upper quadrant soft tissues.	Anterior shoulder stretch. Active thoracic extension. Lateral neck stretches.	Bilateral anterior chest stretch using room corner/door jamb. Sternal lift in sitting with lumbar-thoracic dissociation. Neck stretches in stand/sit.

Correction of the scapular or humeral head position (either by patient active self-correction or therapist manual correction) that improves symptoms during objective assessment tests forms the basis of treatment 1. Initial scapular “setting” exercises allow participants to develop the scapular stability required to ensure an optimal position of the glenoid, hence, a centred humeral head during shoulder motion. Scapular retraining will ideally be taught in a standing position, but since the cohort is likely to be heterogeneous, with varying scapular and humeral head static and dynamic motion deficits, alternative positions, aimed at minimising compensatory strategies, including prone and side-lie may be temporarily adopted. Though varying between individuals, in subjects with SPS, the scapular is frequently downwardly rotated and in anterior tilt [58]; thus, scapular upward rotation exercise drills including “modified shrugs” [59, 60] will be used in this phase to retrain the scapular stabilising muscles.

The rotator cuff strengthening component of the physiotherapy intervention undertaken at treatment 2 and 3 will vary between the groups in terms of the specific type of muscle contraction taught—(i) isometric, (ii) isotonic concentric or (iii) isotonic eccentric (see Fig. 3). Taught in a standardised functional standing position, shoulder at 0°, the dosage will be semi-tailored according to pain severity and irritability, and in keeping with the tendon pathology continuum model [33]. Elastic resistance band will be used for the isotonic exercises (eccentric and concentric), while a rigid band will be used for the isometric exercises to ensure a static position is maintained.

**Fig. 3 Fig3:**
[figure not shown]
Rotator cuff strengthening exercises—between group variation, ER external rotation, IR internal rotation

Treatment 4 will address areas of relative flexibility including the thoracic spine and upper quadrant soft tissues as well as building posterior musculature. For the thoracic spine mobility exercises, retraining may be performed in varying positions, aimed at minimising compensatory strategies. Specific upper quadrant soft tissue flexibility exercises will include a bilateral anterior shoulder/chest stretch and lateral neck flexor stretches. Posterior muscle building will involve standing rows, taught and progressed at 45° and/or 90° determined by individual ability.

Throughout Phase 1, home exercises based on the treatment intervention will be given with exercise progression as per individual response to load, aiming to maximise training effects. These will be performed independently and daily, dose dependent on exercise type. Participants will be provided with an exercise manual. Figure 4 outlines the Phase 1 home exercise program for the isometric group with the programs for the concentric and eccentric groups available as supplementary material [Additional files 1 and 2].

**Fig. 4 Fig4:**
[figure not shown]
Phase 1 home exercise program—isometric group

To standardise treatment as much as possible and since this study is primarily focussed on exercise intervention, manual therapy techniques will not be routinely used. Consistent with the usual clinical care of patients with this shoulder disorder, for individual participants who are unable to progress beyond an exercise stage without manual therapy to facilitate, this will be undertaken but kept to a minimum and recorded.

Phase 2 of the treatment intervention commences on completion of the 6-week follow-up assessment, when participants will be provided with an exercise sheet [Additional file 3] designed to progress them from 0° into range (and therefore no longer specific to one or more of the muscle contractions being evaluated in the trial). These exercises are based on the treatment intervention and home program. The patient will be instructed on how to perform the exercises that take them into a higher range of motion, focus on further strength gains and return to function. At week 9, they will attend a one-on-one check-review to ensure compliance with the exercise sheet.

### Data management and analysis

#### Primary outcome: feasibility of a full-scale RCT

Data collected on numbers of eligible participants recruited, numbers randomised via the assessment algorithm, adherence to and compliance with the intervention as well as drop outs lost to follow-up will be analysed as percentages and used to inform the development of a full-scale RCT.

#### Secondary outcomes: shoulder-related symptoms and disability (WORC, SPADI), strength (hand-held dynamometer), pain (NRS/VRS), perceived change (GRCS)

As this is a pilot study, it is not fully powered to determine treatment effects, and any inferential statistics will be used cautiously. Nevertheless, the analysis of between-group changes in secondary outcomes at each of the follow-up time-points may offer insights into possible trends and guide the design of a future full-scale RCT [61]. Similarly, baseline between-group participant characteristics and any associated influence on outcomes may also be observed. All data will be analysed as per-protocol. Analyses of variance (ANOVA) with repeated measures will be undertaken to evaluate trends in between-group changes in secondary outcome scores, with post-hoc analyses using Tukey’s HSD test performed where significant between-group differences are observed. Continuous variables (SPADI, WORC, 11-point NRS, VRS, hand-held dynamometer and GRCS) will be summarised using means and standard deviations, or medians and interquartile range, while categorical variables (gender) will be summarised using frequencies and proportions (and 95% confidence intervals). Analysis will be undertaken using SPSS statistical packages (Version 24, SPSS Inc. Chicago, IL) with estimation of effect sizes and confidence intervals; significance set at *p* < 0.05.

All data will be de-identified with analyses performed by an independent analyst. Groups will be coded and intervention allocation undisclosed so that the analyst is blind to the exercise program being used in any of the groups. Hard data will be stored in a locked cabinet and all soft files held on a password-protected computer accessible only to the research team. The principle investigator will have access to the final datasets. Results will be made available to participants on request and will be published in a peer-reviewed journal.

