### Participants

Participants will be recruited from a physiotherapy outpatient clinic at a large public hospital and two private physiotherapy clinics, all within metropolitan Melbourne, using internal flyers and social media to promote participation. Since SPS is seen in both general and sporting populations, a combination of public and private sector recruitment sites will ensure a broader pool from which to draw participants. Based on a previous study [15] investigating the use of exercise in SPS with an effect size of 0.66 and maintaining a power of 0.80, calculations indicate a minimum of 30 patients would be required in each group for a full-scale RCT. To determine the feasibility for a full-scale RCT, a sample of 36 across the three groups (12 per group) has been chosen for this pilot study. This is approximately 30% of the calculation for a full-scale RCT [39] with an allowance for drop outs. It is anticipated that this sample size will provide the opportunity to observe recruitment rates using the assessment algorithm, adherence to and compliance with the various components of the intervention, number of participants lost to follow-up and number of adverse events; as well as enable preliminary evaluation of clinical outcome trends while saving the costs associated with a full-scale trial.

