### Outcome measures

#### Primary outcome: feasibility of a full-scale RCT

The primary outcome of this study is to determine feasibility for a full-scale RCT. This will involve an evaluation of (a) ease of recruitment (rate and number as well as suitability of the assessment algorithm), (b) adherence to both phases of the exercise intervention including home program compliance and logbook completion, (c) participant non-completion (drop out number and rate) and (d) adverse events (nature and number). The regular monthly research staff meetings will provide an opportunity for continual evaluation to gauge whether the various components of the study work well together as well as allowing collection and monitoring of data relating to the key parameters that have been identified in (a–d) above.

In order to meet the target sample size, it is planned that the recruitment coordinator will achieve a telephone screening percentage of 75%, and the assessors at each site will achieve a clinical assessment screening percentage of 50%; screening will continue until the target population is reached (12 participants per site [38]. As making a diagnosis of SPS is complex [40, 41, 43–45], an assessment algorithm (see Fig. 2) has been designed in order to ensure the appropriate participants are included in this study [42]. Part of the feasibility of this study relates to the ease of use of the assessment algorithm by the assessors, their willingness to use it and its influence on recruitment rates. Calculating the time it takes to recruit will facilitate planning for the full-scale RCT.

Participant adherence will be monitored by recording the number of physiotherapy assessment and treatment sessions attended. For completeness of data collection and improved statistical analysis, we seek to maximise study retention and adherence. In accordance with the Pedro Scale criteria [46], we plan for a retention rate of at least 85%. By keeping the intervention period relatively short to reduce the patient burden as well as by contacting participants to remind them of their treatment and assessment appointments, we anticipate this will be achievable.

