Compliance with the exercise intervention will be monitored via therapist logbook sign off at each treatment session. In studies that have investigated exercise interventions in participants with SPS, adherence to intervention protocols has been reported as 80% and over [47, 48]. We consider this will be achievable in our study with the exercise check-review during week 9, specifically designed to ensure ongoing compliance.

As well as participants recording adverse events in their logbook, further questioning regarding this will be undertaken by the assessor at trial completion. As all groups in this study will undertake an exercise-based intervention only, serious adverse events are not anticipated. Increased short-term pain during and following performance of exercises has been reported in other exercise-based studies [47]. As all of our participants will undergo a structured semi-individualised exercise program, with progression governed by symptoms and stage of tendon pathology, we anticipate minimal reporting of these kinds of minor adverse events.

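### The secondary between-group comparisons name an undefined per-protocol set as their only population, so the estimates meant for the full-scale trial would exclude participants on a post-randomisation variable

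*Protocol article*

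**What the plan says.** In the protocol article, Data management and analysis, the paragraph on secondary outcomes states: "All data will be analysed as per-protocol". The next sentence gives the analysis to which this applies: "Analyses of variance (ANOVA) with repeated measures will be undertaken to evaluate trends in between-group changes in secondary outcome scores". Tukey comparisons, effect sizes and confidence intervals follow. No intention-to-treat or as-allocated population appears anywhere in the article, and nothing says what makes a participant per-protocol. The same paragraph says of the pilot that "it is not fully powered to determine treatment effects, and any inferential statistics will be used cautiously".

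The primary feasibility outcome has its own analysis paragraph, just before, under which "adherence to and compliance with the intervention as well as drop outs lost to follow-up will be analysed as percentages".

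Two planning figures bear on how many participants may be excluded, both under Outcome measures, Primary outcome. On retention, "we plan for a retention rate of at least 85" per cent. On adherence, the article notes that in earlier exercise studies "adherence to intervention protocols has been reported as 80% and over" and considers this achievable here. The sample size is under Participants: "a sample of 36 across the three groups (12 per group) has been chosen for this pilot study".

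The last paragraph of the Background says that the clinical outcome data are to support sample size estimation for a full-scale trial. The Discussion says that they may give preliminary effect sizes and better power calculations.

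**The concern.** Completing and adhering to the programme are settled after randomisation. The arms differ in the contraction type taught in sessions 2 and 3 and practised at home in Phase 1. Progression follows symptoms, and the article anticipates that the isometric arm may have more immediate relief of pain. It is therefore plausible, though not shown, that the arms will differ in who stops or falls short. An analysis restricted to those who complied then compares groups that randomisation no longer balances.

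At stake are the numbers the pilot hands on. A shifted arm mean would misdirect the view of which contraction type looks promising. An SD taken from a selected group would make standardised effects too large and the next trial too small. A missing definition alone could be left to a fuller document. The choice of population is different, because the article makes it explicitly.

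**Working it through.** **The plan's own figure.** The only calculated figure is 30 per group for the full-scale trial, "with an effect size of 0.66 and maintaining a power of 0.80". A three-group ANOVA with f = 0.66/2 = 0.33 at alpha 0.05 needs 30.5 per group. A one-sided two-group t-test needs 29.1, so 30. A two-sided two-group t-test needs 37. The article does not say which was used. The present point does not depend on it; 0.66 serves below only as a yardstick, read as a standardised mean difference.

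**Step 1: size of the per-protocol set.** Inputs: 36 randomised, 85% retention, 80% adherence. Assumptions: adherence is read as the share of completers who count as adherent, and per-protocol excludes drop-outs.
- As allocated: 36, or 12 per group.
- Retention only: 36 × 0.85 = 30.6, about 10 per group.
- Retention and adherence: 30.6 × 0.80 = 24.5, about 8 per group.
- Left out: 36 − 30.6 = 5.4 (15%) to 36 − 24.5 = 11.5 (32%).

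**Step 2: one arm loses its worst responders.** Assumptions, none from the article: normal outcomes, SD 1, no true difference, 3 of 12 (25%) excluded in one arm and none in the others.
- Removing the lowest fraction p raises the mean by φ(z_p)/(1 − p). For p = 0.25, z = −0.674 and φ = 0.318, so the shift is 0.318/0.75 = 0.424 SD. That is 0.424/0.66 = 64% of the planning effect.
- With exactly 12 participants and the worst 3 dropped, the expected shift is 0.39 SD (0.39/0.66, about 60%).
- If exclusion correlates only 0.5 with outcome: 0.5 × 0.424 = 0.21 SD.

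**Step 3: both arms lose participants, at rates 20 points apart.** Same assumptions otherwise. Simulated differences between two arms with no true effect:

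| Exclusion rates | Correlation 0.5 | Entirely by outcome |
|---|---|---|
| 5% and 25% | 0.16 SD | 0.31 SD |
| 12% and 32% | 0.15 SD | 0.30 SD |

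**Step 4: equal exclusion in the arms.** The simulated difference is about zero, but the SD, truly 1, falls. Required n is proportional to SD², so a full-scale calculation that used the reduced SD with an unchanged mean difference would give this fraction of the proper n:

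| Excluded per arm | SD, correlation 0.5 | SD, entirely by outcome | Fraction of proper n |
|---|---|---|---|
| 15% | 0.95 | 0.80 | 0.95² = 0.90; 0.80² = 0.64 |
| 32% | 0.93 | 0.69 | 0.93² = 0.86; 0.69² = 0.48 |

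**Step 5: scale against sampling error.** With 12 per arm, the standard error of a difference between two arms is √(2/12) = 0.41 SD. The extreme case in Step 2 is about one standard error and the moderate case about half of one.

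**The case against.** The strongest reply is that little rests on these comparisons. They are secondary outcomes in a 36-patient pilot that says itself it is underpowered and will interpret cautiously, and even the extreme scenario is no larger than one standard error. This stands as a limit on importance. It does not remove the point: caution about p-values does not correct a selected mean or SD, and those are what the pilot passes on.

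Three further objections hold in part.
- The immediate pain and strength changes are measured before and after one set of contractions in sessions 2 and 3. Later drop-out or poor home compliance need not touch them, so the exposure is mainly at weeks 6 and 12 and, for WORC and SPADI, the 6-month postal review.
- No passage shows that adherence will differ by arm. All arms exercise, progression follows symptoms in each, and Phase 2 is not group-specific. Differential exclusion is possible, not established.
- Naming an intention-to-treat population does not recover outcomes that were never collected, and a standard repeated-measures ANOVA drops incomplete cases anyway. The remedy has to deal with this.

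The phrase might also be a loose way of saying that data are analysed as the protocol lays down. Then no population is stated at all, and readers will still take the usual meaning.

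A reader might infer that the sentence removes drop-outs and non-adherers from the feasibility results, or contradicts the primary outcome because it speaks of all data. The article does not support that. The sentence stands under the secondary outcomes, and the separate feasibility paragraph counts adherence and drop-outs as percentages. Nor can one say that the estimates would fail to match the full-scale trial's analysis population, because the article does not state what that will be.

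**Conclusion.** The point holds for the secondary between-group comparisons, mainly the longer-term ones. The article fixes an undefined per-protocol set as their only population, and so selects on a post-randomisation variable that the arm may affect, in estimates that it intends for full-scale planning. Between 15% and 32% of those randomised could be left out, the upper figure resting on the reading of adherence in Step 1.

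The size of any bias cannot be known from the article. The shifts of about 0.4 SD (extreme) and 0.2 SD (moderate), and the SD reductions, are hypothetical scenarios under assumed normal outcomes and assumed exclusion patterns, not predictions. The point should be fixed, because the change is cheap and outcomes not collected after a participant stops may be hard to recover. It does not threaten the pilot's primary feasibility aim.

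**What to change.** Replace the sentence with wording such as: *The main between-group analysis of the secondary outcomes includes all randomised participants in the arm to which they were allocated, using all available outcome data in a likelihood-based mixed model for repeated measures. Planned outcome assessments are still sought from participants who stop exercising, where they agree. A per-protocol set, defined before the data are analysed, is used for a sensitivity analysis.*

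The mixed model takes the place of the complete-case repeated-measures ANOVA, so that a participant with a missing visit still contributes the others. It relies on missingness being explained by the observed data, which should be stated. The global rating of change, collected only at week 12, can be compared as allocated among those who answer. The feasibility paragraph needs no change on this account.

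Cost: a short change of text, one extra analysis run, and some outcome follow-up of participants who stop exercising. No new outcome measure is needed.
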